## **7.8 Study Sites SAE Reporting Requirements**

All deaths and life-threatening SAEs reported as above will be reported to the main PI on the study within 3 business days. SAEs that are possibly, probably, or definitely related to the research will be reported to the NIAID IRB within 7 days of investigators awareness, regardless of expectedness. The main PI (NIAID) will report SAEs and AEs reported during this study to all sites at the time of continuing review.

In Korea, local PIs have a responsibility to report AEs to each IRB and if needed, to MFDS.

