## 4 Subject Enrollment

### 4.1 Accrual

Subjects with diagnosed pulmonary TB who have elected to undergo lung lobectomy will be given the opportunity to participate in the study. We expect accrual to take approximately 12 months among the three study centers of Asan Medical Center, National Medical Center, and Pusan National University Hospital.

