## **7.7 Study Sites AE Reporting**

Since the subjects on this protocol will be seen because of illness, and are likely to be ill at baseline, many will have AEs by the above criteria. However, their medical management will be standard of care for those illnesses and complications and not part of the research process. Therefore, AEs associated with the underlying disease will not be recorded as AEs. However, AEs assessed to be related to the research will be recorded as such. As described below, all SAEs will be recorded and reported.

Any grade 3 or 4 AE (as defined in Section 7.1) that is possibly, probably or definitely related to study drugs and occurs between the times a subject signs the informed consent form and the time s/he completes the planned surgery (or at the time of early discontinuation of the subject from study participation for any reason) will be captured and recorded and reported with continuing annual review.

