## **7.9 Adverse Event Reporting to the NIAID, Asan, National Medical Center, and Pusan Institutional Review Boards and RCHSPB Safety**

As stated above, all sites will report directly to the main PI at the NIAID. Each site must also report to their respective IRBs. The NIAID site must in addition report to RCHSPB Safety. Details of reporting are described in the sections below. Respective reporting will be made by telephone, fax or email to the appropriate addresses.

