#### **7.9.1.2 Annual Reporting to the NIAID IRB**

The following items will be reported to the NIAID IRB in summary at the time of Continuing Review:

- All unanticipated problems, including AEs and non-AEs
- Expected serious adverse events that are possibly, probably, or definitely related to the research
- Serious adverse events that are not related to the research
- All protocol deviations which in the opinion of the investigator should be reported.
- Any trends or events which in the opinion of the investigator should be reported

(Protocol violations and deviations mentioned above are defined in the monitoring entity policy.)

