### **7.9.3 Asan Site Reporting to the Asan IRB**

In addition to reporting to the NIAID PI (as above), Asan investigators should report all reportable SAEs and AEs to the Asan IRB and the director as promptly as possible within the time period described as follows:

- 1) For the cases at Asan, ALL SAEs at occurring at Asan should be reported to the Asan IRB within one business day of the investigator's awareness. .
- 2) Serious and unexpected Adverse Drug Reactions at other sites that lead to death or are life-threatening must be reported to the AMC IRB within 7 business days of AMC's awareness. Other ADRs from other sites should be reported to the AMC IRB within 15 days of AMC's awareness.

The sponsor must provide continuing report until the AE comes to an end (loss of this adverse reaction or when it is impossible to do the follow up investigation).

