### **7.9.4 PNUH Site Reporting to the PNUH IRB**

In addition to reporting to the NIAID PI (as above):

- 1) PNUH Investigators must provide a report to the PNUH IRB within 24 hours after becoming aware of a subject death or a potentially life-threatening serious adverse event at occurring at PNUH. Any other SAEs at occurring at PNUH should be reported to the PNUH IRB within 7 days of the investigator's awareness.
- 2) Any other SAEs occurring at other sites must be reported to PNUH IRB within 15 days after the PNUH investigator's awareness.
- 3) Protocol violations which the investigator decides are important will be reported to the PNUH IRB within 7 days of the PNUH investigator's awareness. Other protocol violations will be reported to the PNUH IRB quarterly.

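### Sites are told of each other's serious adverse events at annual continuing review, so the short reporting deadlines for other-site events in 7.9.3 and 7.9.4 have no defined trigger

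*Protocol*

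**What the plan says.** **Reports from the sites upward.** Under Protocol 7.9, "all sites will report directly to the main PI at the NIAID". Section 7.8 sets a clock for the gravest events: "All deaths and life-threatening SAEs reported as above will be reported to the main PI on the study within 3 business days". Related SAEs of any kind are due at the NIAID IRB within 7 days of investigator awareness (7.8 and 7.9.1.1).

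**Reports from the main PI back to the sites.** Section 7.8 gives one rule: "The main PI (NIAID) will report SAEs and AEs reported during this study to all sites at the time of continuing review". Two places show that this review is yearly. Section 7.7 says that related grade 3 or 4 events "will be captured and recorded and reported with continuing annual review". Section 7.9.1.2, which lists the items for continuing review, is headed "Annual Reporting to the NIAID IRB".

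**Duties of one site for events at another.**
- Asan (7.9.3): "Serious and unexpected Adverse Drug Reactions at other sites that lead to death or are life-threatening must be reported to the AMC IRB", with 7 business days allowed from Asan's awareness. Other drug reactions elsewhere have 15 days, also from Asan's awareness.
- PNUH (7.9.4): "Any other SAEs occurring at other sites must be reported to PNUH IRB within 15 days after the PNUH investigator's awareness".
- NMC (7.9.5): other-site unanticipated problems are reportable when they force a change to the protocol or consent form. No clock is given.

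**Related provisions.** Section 10 has the PI report unanticipated problems involving risk promptly to the IRBs. On duration, section 4.1 says: "We expect accrual to take approximately 12 months among the three study centers".

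**The concern.** Every subject at every hospital receives the same five drugs within hours of lung resection, and 10.3.1 says that participation brings no benefit. A serious related reaction at one hospital therefore bears directly on the next consent discussion at the other two.

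Reports travel up to NIAID in days, but the one stated return route to the sites is yearly. The Asan and PNUH rules were plainly written on the footing that these sites learn of such events soon after they happen. A 7-business-day or 15-day clock that starts on receipt of an annual report does no expedited work. The protocol thus sets local duties without saying what starts them.

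There is a smaller gap in the upward direction. Only deaths and life-threatening SAEs have a deadline for reaching the main PI. A related hospitalisation or disability has none, although the 7-day clock to the NIAID IRB applies to it too.

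**Working it through.** The plan gives no figure to reproduce. The check sets the reporting rules side by side and then sizes the delay.

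**1. Which event reaches whom, and when**

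| Route | Event | Stated time | Source |
|---|---|---|---|
| Site to main PI | Death, life-threatening SAE | 3 business days | 7.8 |
| Site to main PI | Other related SAE | none stated | 7.8, 7.9 |
| To NIAID IRB | Related SAE | 7 days | 7.8, 7.9.1.1 |
| NIAID to RCHSPB Safety | Death, potentially life-threatening SAE | 7 days from NIAID awareness | 7.9.2 |
| PI to IRBs | Unanticipated problem involving risk | promptly, no number | 10 |
| Main PI to all sites | SAEs and AEs | continuing review | 7.8 |
| Asan to its IRB | Other-site fatal or life-threatening unexpected reaction | 7 business days from own awareness | 7.9.3 |
| Asan to its IRB | Other reactions at other sites | 15 days from own awareness | 7.9.3 |
| PNUH to its IRB | Other-site SAE | 15 days from own awareness | 7.9.4 |

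No row gives an expedited notice from the main PI to a site investigator. The Asan and PNUH rows depend on such a notice.

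**2. What section 10 covers**

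Under 6.1 an unanticipated problem must be unexpected, at least possibly related, and a source of greater risk than was known. All three conditions apply. An adverse event is expected if the protocol, consent document or package insert lists it as possibly related. Section 6.6.1 lists nephrotoxicity and ototoxicity for KM and QT prolongation for MXF. A serious related reaction of a listed kind, with no surprise in severity or frequency, therefore falls outside section 10 and is left to the 7.8 rule.

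**3. Size of the delay**

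Inputs: 15 subjects (5.2), accrual of about 12 months (4.1), review every 12 months (7.7, 7.9.1.2). Assumptions: even accrual, and an event at a random time.

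- Accrual rate: 15 / 12 = 1.25 subjects per month.
- Longest wait between reviews: 12 months. Average wait: 12 / 2 = 6 months.
- Subjects enrolled during an average wait, if accrual runs throughout it: 1.25 × 6 = 7.5, so about 7 to 8.
- Upper bound (event in the first subject, no review before the last): 15 − 1 = 14.

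**4. Sensitivity**

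The 7.5 applies when no review falls within accrual. If a review falls r months into accrual, the average number enrolled after the event, up to the next review or the end of accrual, is 1.25 × [r² + (12 − r)²] / 24. With r = 12 this is 1.25 × 144 / 24 = 7.5. With r = 6 it is 1.25 × 72 / 24 = 3.75.

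These counts include the hospital where the event occurred, which already knows. If the three sites accrue equally (assumption), the two uninformed sites account for 7.5 × 2/3 = 5. Enrolment may also exceed 15, since it continues until each time point has three evaluable subjects (3.1, 3.3).

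**The case against.** Section 7.8 does not say that continuing review is the sole contact between the main PI and the sites. Its sentence takes SAEs and AEs together and can be read as a cumulative summary. The other-site duties in 7.9.3 and 7.9.4 themselves presuppose earlier knowledge. Section 10 requires prompt reporting of unanticipated problems and names all four IRBs. An unexpected related death would normally qualify, since 6.6.1 lists no fatal outcome. Central bodies are told within days, every site needs NIAID approval to run the protocol, and every enrolment passes through one central organisation (4.5, Randomization).

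Much of this stands, and it rules out some stronger readings. A reader might infer that the hospital IRBs cannot act on a related death elsewhere; section 10 speaks against that. A reader might also infer that a reaction would stay unknown for the whole accrual period while 14 more subjects are dosed. That needs the event in the first subject, no review within accrual, and no action by central bodies that already know. Approval must precede implementation, so an annual review counted from approval (an assumption) would fall within a 12-month accrual or at its end. Nor does the trigger problem extend to a missed deadline at NMC, because 7.9.5 sets no clock for other-site events. The RCHSPB clocks run from NIAID's own awareness, so the missing upward deadline does not make them impossible to meet.

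The objection does not supply the missing trigger. Section 10 gives no number of days, does not say whether the main or a local PI reports, and does not name the investigators who consent and dose. It leaves out serious related reactions that are already expected. Reading 7.8 as a summary only means that the protocol states no prompt route at all.

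**Conclusion.** The point holds as a gap between sections of the protocol that must be reconciled. The one stated report from the main PI to the sites is annual, and the awareness-based duties in 7.9.3 and 7.9.4 therefore lack a defined trigger. The gap is clearest for serious related reactions already listed as expected, and for direct notice to site investigators.

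The average wait is about 6 months. With no review inside accrual, about 7 to 8 further subjects would be enrolled across all sites in that time; with a review halfway through, about 4. These figures assume even accrual and a random event time, and they describe what the written rule permits. They do not predict that informed central bodies would stay silent. Severity: should be fixed. Central oversight and section 10 give partial protection, but the remedy is simple and concerns subject safety.

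**What to change.** Amend section 7.8 as follows:

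1. The main PI forwards each SAE judged possibly, probably or definitely related, and each unanticipated problem, to all three site investigators on a stated short clock. The sponsor sets the number of days so that the duties in 7.9.3 and 7.9.4 start promptly.
2. Continuing review keeps the cumulative summary of SAEs and AEs.
3. Related SAEs that are not life-threatening get a deadline for reaching the main PI that fits within the 7-day NIAID IRB clock.

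State in 7.9.3 and 7.9.4 that receipt of the main PI's notice counts as awareness, if the site has not learned of the event sooner. In section 10, say which PI reports unanticipated problems and within what time.

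The cost is one amended paragraph with matching edits, IRB review of the amendment, and an e-mail per event in a study of about 15 subjects. No subjects or procedures are added, and no analysis changes.

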## **7.9 Adverse Event Reporting to the NIAID, Asan, National Medical Center, and Pusan Institutional Review Boards and RCHSPB Safety**

As stated above, all sites will report directly to the main PI at the NIAID. Each site must also report to their respective IRBs. The NIAID site must in addition report to RCHSPB Safety. Details of reporting are described in the sections below. Respective reporting will be made by telephone, fax or email to the appropriate addresses.

### **7.9.1 PI reporting to the NIAID IRB**

#### **7.9.1.1 Expedited Reporting to the NIAID IRB**

Unanticipated problems that are either AEs or non-AEs (as defined above) and Protocol Violations will be reported within 7 calendar days of investigator awareness. SAEs that are possibly, probably, or definitely related to the research will be reported to the NIAID IRB within 7 days of investigators awareness, regardless of expectedness.

All deaths will be reported within 7 calendar days of investigator awareness.

#### **7.9.1.2 Annual Reporting to the NIAID IRB**

The following items will be reported to the NIAID IRB in summary at the time of Continuing Review:

- All unanticipated problems, including AEs and non-AEs
- Expected serious adverse events that are possibly, probably, or definitely related to the research
- Serious adverse events that are not related to the research
- All protocol deviations which in the opinion of the investigator should be reported.
- Any trends or events which in the opinion of the investigator should be reported

(Protocol violations and deviations mentioned above are defined in the monitoring entity policy.)

### **7.9.2 PI reporting to RCHSPB Safety**

- 1) The NIAID PI is responsible for reporting to RCHSPB Safety.
- 2) NIAID Investigators must report to RCHSPB Safety within 7 days after becoming aware of a subject death or a potentially life-threatening serious adverse event.
- 3) NIAID Investigators must report to RCHSPB Safety within 15 days after becoming aware of an inpatient hospitalization (other than elective) or a persistent or significant disability/incapacity which fits the reporting requirements.
- 4) NIAID Investigators will report within 15 days any other event or condition regardless of grade, which in their judgment represents an event reportable to RCHSPB Safety.

### **7.9.3 Asan Site Reporting to the Asan IRB**

In addition to reporting to the NIAID PI (as above), Asan investigators should report all reportable SAEs and AEs to the Asan IRB and the director as promptly as possible within the time period described as follows:

- 1) For the cases at Asan, ALL SAEs at occurring at Asan should be reported to the Asan IRB within one business day of the investigator's awareness. .
- 2) Serious and unexpected Adverse Drug Reactions at other sites that lead to death or are life-threatening must be reported to the AMC IRB within 7 business days of AMC's awareness. Other ADRs from other sites should be reported to the AMC IRB within 15 days of AMC's awareness.

The sponsor must provide continuing report until the AE comes to an end (loss of this adverse reaction or when it is impossible to do the follow up investigation).

### **7.9.4 PNUH Site Reporting to the PNUH IRB**

In addition to reporting to the NIAID PI (as above):

- 1) PNUH Investigators must provide a report to the PNUH IRB within 24 hours after becoming aware of a subject death or a potentially life-threatening serious adverse event at occurring at PNUH. Any other SAEs at occurring at PNUH should be reported to the PNUH IRB within 7 days of the investigator's awareness.
- 2) Any other SAEs occurring at other sites must be reported to PNUH IRB within 15 days after the PNUH investigator's awareness.
- 3) Protocol violations which the investigator decides are important will be reported to the PNUH IRB within 7 days of the PNUH investigator's awareness. Other protocol violations will be reported to the PNUH IRB quarterly.

#### **7.9.5 NMC Site Reporting to the NMC IRB**

In addition to reporting to the NIAID PI (as above) local investigators should quickly report all serious and unexpected adverse events related to study design, study intervention, and/or study agent/device within the following timeframe:

- 1) Local investigators must provide a preliminary report to the NMC IRB within 7 days after becoming aware of a subject death or a potentially life-threatening adverse event. A detailed report should follow within 8 days after the initial report. If a death is reported, the additional information, such as the autopsy report (if performed) and death certificate, should be provided at this time. In addition, these items will be reported to NMC IRB at the time of Continuing Review.
- 2) Local investigators must provide a report to the local IRB within 15 days after becoming aware of any other unexpected adverse events which are serious in nature.
- 3) Investigator must provide follow up report until the AE comes to an end (resolved or impossible to follow up).

Reporting requirements of an unanticipated problem (UP) which harms the subject(s) and/or others:

- 1) Local Investigator must report the following items to the IRB within 7 days of awareness.
  - a) New information which negatively affects the safety of the subject(s) or the conduct of clinical trial
  - b) Changes which have a significant impact on the conduct of clinical trial or places subject(s) at a greater risk of harm.
- 2) Investigator should describe any corrective action initiated during the study in order to protect the subject(s) from potential or further damage and to prevent a recurrence of the problem.
- 3) Other UPs will be reported to the NMC IRB in summary at the time of Continuing Review. If not applicable, it is possible to describe simply in summary as 'there was no UP'.

In the case of a multicenter trial, if the protocol or informed consent form needs to be changed due to UPs from other sites which increase the risk for the subjects, the UP(s) should be reported to NMCIRB.

## **8 Data Management Plan---Data Collection, Sample Storage and Publication**

### **8.1 Data Collection**

Study data will be collected on standardized paper CRFs prepared in conjunction with the RCHSPB of NIAID/NIH and the NIAID study team. The local study team will use only NIAID-approved CRFs. The PI is responsible for assuring that the data collected is complete, accurate, and recorded in a timely manner. The CRFs will be collected and placed into a subject-specific binder. Source documentation (the point of initial recording of a piece of data) should support the data collected on the case report form, and be signed and dated by the person recording and/or reviewing the data. Source documents include all recordings of observations or notations of clinical activities and all reports and records necessary for the evaluation and reconstruction of the clinical trial. Source documents include, but are not limited to, the subject medical records, electronic chart records, laboratory reports, electrocardiogram (EKG) tracings, x-rays, radiologist reports, biopsy reports, ultrasound photographs, subject progress notes, pharmacy records and any other similar reports or records of procedures performed during the subject's participation in the protocol. Data for CRFs will be collected during subject visits by health care providers and abstracted from the medical record. Once the data is collected, it will be reviewed by the RCHSPB monitoring team or their contractors. Once reviewed, a copy of each CRF will remain at the site while the original will be retained by the monitoring team and a copy sent to the NIAID investigators. Any data that is compiled for statistic or other manipulation will be handled in an Access database. The scientific results from this study will require various formats, depending on the data type. Locked copies of these files containing the results will be compiled by the research supervisor and made available to monitoring and regulatory agencies as necessary.

HRCT and Dynamic MRI image files will be transferred to the ITRC team and will then be transferred to NIAID. The radiology analysis team at NIAID will access these stored records to perform their analysis. The results of the analysis will include numerical and image output that will be deposited into the TBRS database.

Case Report Forms (CRFs) will be filled out by the health care providers. Information for the CRFs will be obtained from the subject interview upon consent, medical records, and data accrued in the trial, and will include a medical history, lab results and specimen data, and scan results obtained in the trial.

### **8.2 Data Management**

Data entered onto the CRF will be entered into an access database, which will be managed and monitored by the ITRC-NIH team. Access to the database is password controlled and will be limited to those with data entry and management responsibilities. Records are protected by ownership control and a complete log of all activities within the system is recorded. All study related data will be maintained on servers located at ITRC and NIH and image files will be stored and indexed in the system.

### **8.3 Data Storage**

All essential documentation for all study subjects including history and physical findings, laboratory data, and results of consultations are to be maintained by the investigators in a secure storage facility for a minimum of three years. These records are to be maintained in compliance

with IRB/EC (Institutional Review Board/Ethics Committee), local and government requirements, whichever is longest. All records are to be kept confidential to the extent provided by law.

#### **8.4 Publication of Research Findings**

Collaborating protocol team members will own the data generated by or resulting from this project, and they may arrange for publication of this original research (with consent of all study investigators) in a primary scientific journal, and for copyright by the journal unless the journal's copyright policy would preclude individuals from making or having made a single copy of any such article for their own use.

